Thus, although previous research has suggested a trend towards increased anxiety and distress associated with HPV-positive results, the psychological impact is not clear in the context of HPV primary testing, where communication of HPV results to all women entering the programme will be routine and there will be far greater numbers of women receiving hrHPV-positive results compared with HPV triage for low-grade and borderline cytology. Previous research has indicated poor knowledge and understanding of the link between HPV and cervical cancer, and between HPV and sexual activity, among women in the UK.^14–18^ Therefore, if the meaning of HPV results and cancer risk are not well understood, this has the potential to induce unnecessary anxiety. This is particularly relevant for women who are told that they are HPV positive with normal cytology results given that, under the new algorithm, they will be aware that they have hrHPV but there will be no further clinical investigation for 12 months. The likelihood of this subgroup developing cervical cancer in the interim period is extremely low. However, it is possible that women may still feel anxious and/or distressed. Anxiety and distress may be accentuated if women do not fully understand the meaning of these test results. In the light of the high prevalence of HPV, especially in younger women (under 30 years),^19^ it is expected that a large number of women will fall into this new 12-month recall category. In order for the NHSCSP to achieve the sensitivity gains of switching to HPV primary testing, it is important that women in this group attend their recall appointment at 12 months without experiencing significant anxiety in the interim.

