## Methods and analysis

### Design

A cross-sectional between-groups design will be employed to assess women at baseline (shortly after receiving their screening result), 6 months postscreening result and 12 months postscreening result.

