### Participants and eligibility

Participants will include women aged 25–64 years who have taken part in the NHSCSP in one of five sites where HPV primary testing has been introduced: North London, Sheffield, Norfolk and Norwich, Liverpool and Manchester NHS Trusts.

Eligible women will include those who have received test results within the recruitment period at each NHS site (∼12 weeks recruitment at each).

We will recruit three groups of women following their first HPV test, including those who test negative for HPV, those who are HPV positive with normal cytology and those who are HPV positive with abnormal cytology (groups 1 to 3 in table 1). In addition, we will recruit two groups of women who had initially tested positive for HPV with normal cytology, and who have recently attended their 12-month follow-up appointment, including women who have persistent HPV, and those who tested HPV negative at the recent test (groups 4 and 5 in table 1). We will also recruit a control group of women who have been screened using cytology only and have received a normal result (the participating sites have not yet introduced HPV primary screening for all women). This means there will be a total of six possible combinations of HPV and cytology results for eligibility in this study (six recruitment groups). See table 1 for an overview.

**Table 1 BMJOPEN2016014356TB1:** HPV and cytology results for the six groups included in the study

	HPV result	Cytology result
Group 1	Negative	Not tested
Group 2	Positive	Normal
Group 3	Positive	Abnormal
Group 4*	Persistent positive at 12 months	Normal
Group 5*	Negative at 12 months	None
Group 6 (control)	None	Normal

*Women in groups 4 and 5 will all have tested HPV positive with normal cytology at their first screen and will be recruited to the study after their 12-month follow-up test.

HPV, human papillomavirus.

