### Procedures

Eligible patients will be identified by members of staff in cytology departments in NHS laboratories at each of the participating sites. University College London (UCL) will communicate numbers needed in each group to each laboratory as the study progresses, proportionate to the numbers of results processed at each laboratory.

NHS staff will allocate each potential participant a unique identity number, and link this to the patient's name and address. Section 251 approval has been granted to the NHS to upload this information to a secure printing and mailing company (CFH Docmail) for the purposes of contacting participants. Docmail is contractually bound to comply with the Data Protection Act (1998) and securely destroy these data within 30 days of receipt.

Potential participants will be mailed invitation packs to their home address. Invitation packs will include an invitation letter, participant information sheet, consent form and a baseline questionnaire booklet. If participants have not returned the questionnaire after 3 weeks, Docmail will send a reminder pack containing the same documents. Those who opt to take part can do so by returning a completed consent form and questionnaire booklet to UCL.

Participants will also be mailed postal questionnaire packs at 6 and 12 months follow-up. Again, they will be sent a reminder pack containing a reminder letter and another copy of the questionnaire 3 weeks later.

Data from NHS clinical records:

Patient age, index of multiple deprivation score (derived from postcode), date of most recent cervical screen, date of last (previous) cervical screen, number of previous cervical screens and test results will be transferred as population data to UCL from each NHS site for all potential participants approached, with the exception of patients who have opted out. These data will contain no identifiable information; data will be pseudonymised using unique identity numbers. These additional data sets will include survey non-responders to allow for examination of response biases in relation to demographic and screening factors.

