### Descriptive measures

Age, ethnicity, marital status, index of multiple deprivation (a measure of deprivation linked to an individual's residential postcode), education level, NHS site, previous screening history and HPV vaccine status will be collected for descriptive information and as potential control factors. See table 4 for an overview.

**Table 4 BMJOPEN2016014356TB4:** Descriptive outcome measures

Measure	Description	Source
Demographics	Ethnicity, educational attainment, employment and marital status will be assessed via questionnaire. Age of participant will be communicated to UCL from participating laboratories at pilot sites. This will be measured at baseline.	Self-reported in questionnaire. Age at baseline, communicated to UCL from NHS clinical records.
Index of multiple deprivation	Index of Multiple Deprivation score (IMD) will be assigned to participants by laboratories and communicated to UCL. The IMD is a measure of area level deprivation which can be derived from a postcode.^26^ It takes into account: income deprivation; employment deprivation; education, skills and training deprivation; health deprivation and disability; crime; barriers to housing services; and living environment deprivation.	Calculated by the NHS via clinical records and communicated to UCL in score form.
NHS Site	The NHS site where women are screened and receive test results will be recorded via communication from participating laboratories.	Communicated to UCL by NHS site.
Previous screening history	Previous screening history will be communicated to UCL from participating laboratories. This information will include date of last screening and number of previous screenings.	Communicated to UCL from NHS clinical records.
HPV vaccine status	Participants will be asked to indicate whether they have received the HPV vaccine and how many doses they had. This will be measured at baseline.	Self-reported by participant in questionnaire.

HPV, human papillomavirus; NHS, National Health Service, UCL, University College London.

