### Data analyses and statistics

Data will be coded and analysed using SPSS, R and Stata. An α level of p<0.05 will be used throughout.

Preliminary analyses (analysis of variance (ANOVAs) and χ²) will be conducted to explore descriptive statistics and to identify significant group differences, as potential control measures, for age, index of multiple deprivation, pilot site, screening result, previous screening history, HPV vaccine status, marital status, ethnicity and educational attainment. Primary analyses will comprise between-groups ANOVAs to explore whether anxiety and general distress differ between screening result groups shortly after initial presentation of screening result (baseline).

Mixed ANOVAs will be conducted to explore whether differences in anxiety and general distress are observed between screening result groups over time (baseline, 6 months and 12 months).

General linear modelling will be conducted to consider whether understanding of screening results, knowledge of HPV, perceived risk of developing cervical cancer, concern about screening result, psychosexual functioning and intention to engage in future screening differ between screening result groups for secondary analyses.

Health-related quality of life data will be analysed in the health economic cost-effectiveness evaluation (not as part of this psychological evaluation).

Post hoc comparisons will be conducted where appropriate and effect sizes will be calculated.

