## Discussion

This psychological evaluation of HPV primary testing within the NHSCSP will provide evidence about the psychological consequences of testing positive for HPV in this context and is expected to show that the negative consequences are minimal and short-lived, as has been found when HPV testing is used to triage women.^11^
^12^ The findings should help identify any unmet information needs of women taking part in the programme. If adverse psychological effects are observed, the results will help to inform the development of materials and/or procedures aimed at ensuring clarity in the meaning of test results and reducing psychological burden. Given that a ministerial announcement has now been made, stating that HPV primary screening is to be rolled out across England and incorporated into routine NHS practice,^9^ the study findings are likely to directly inform finalised NHSCSP test invitation letters, result letters and accompanying HPV information materials. They may also help inform the development of pragmatic interventions (eg, training programmes, written information) for healthcare professionals working in cervical screening, to promote effective communication and address common concerns for women undergoing HPV primary screening.

In addition, we will be gathering certain population-level data from NHS databases on all women approached to take part in this study, including index of multiple deprivation score, age, test results and cervical screening history. From this information, along with questionnaire data collected from study participants, we will explore predictive relationships between outcomes. This may help identify certain groups of women likely to need additional support. For example, previous research has suggested that younger age and lower understanding of the meaning of test results predicts higher anxiety among women who are HPV positive.^11^ In the context of HPV primary testing, if results indicate similar patterns, this may highlight groups of women requiring additional information and/or interventions to minimise any adverse psychological effects.

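### Control variables for the non-randomised primary comparison are chosen by preliminary significance tests and never fixed in the model, although the protocol gives prior reason to suspect age as a confounder

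*Protocol article*

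**What the plan says.** The Design section describes a comparison of naturally occurring groups: "A cross-sectional between-groups design will be employed to assess women at baseline" and at two later times. Membership of the six groups follows from the HPV and cytology results (Participants and eligibility, Table 1).

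Under Descriptive measures, age, deprivation, site and the other background variables "will be collected for descriptive information and as potential control factors". Under Data analyses and statistics, preliminary ANOVAs and chi-square tests are run "to identify significant group differences, as potential control measures, for age, index of multiple deprivation, pilot site" and further variables, with one significance level of 0.05 for all tests. The same paragraph then defines the main test: "Primary analyses will comprise between-groups ANOVAs to explore whether anxiety and general distress differ between screening result groups" at baseline. No covariate is named there, and no sentence says what happens to a variable once it is flagged.

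Two other sections bear on age. The Introduction refers to the "high prevalence of HPV, especially in younger women (under 30 years". The Discussion reports that previous research has suggested that "younger age and lower understanding of the meaning of test results predicts higher anxiety among women who are HPV positive".

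**The concern.** In a non-randomised comparison, the variables that could confound it have to be decided on subject-matter grounds. A p-value for group imbalance does not do that job. It ignores how strongly the variable predicts anxiety, and it depends on sample size. A modest imbalance in a strong predictor can be passed over, while a large imbalance in an irrelevant variable is kept.

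For age, the reason to adjust is known before any data arrive. The protocol says that HPV is common particularly in younger women and cites evidence linking younger age to anxiety among HPV-positive women. Eligibility runs from 25 to 64 years, so age gaps between the result groups have room to arise.

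The second weakness is that the variables are only potential controls. An analyst could follow the text exactly and report an unadjusted primary result, or could settle the covariates after seeing the data. Either way, part of a group difference in STAI-6 or GHQ-12 might reflect age and be credited to the HPV result. The Discussion expects the findings to inform result letters and information materials.

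**Working it through.** **Inputs from the protocol (Sample size).** f = 0.14, alpha 0.05, N = 673, power 80%; STAI-6 means of 36 to 40 (a 4-point range), SD 12; 3415 women approached, 35% initial response, then 75% and 75% retention. Six groups (Table 1).

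**The plan's own figure.** One-way ANOVA, six equal groups, noncentral F with λ = f²N. Power at N = 673 is 0.809, and 80% power needs N = 661, so 673 is reproduced to within 2%. It is the sample size of an unadjusted six-group ANOVA. Retention: 3415 × 0.35 × 0.75 × 0.75 = 672. The baseline comparison has 3415 × 0.35 = 1195 responders, about 199 per group.

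**Assumptions, not in the protocol.** No true effect of the screening result; groups 2, 3 and 4 younger by 5 to 10 years; an age slope of 0.05 to 0.2 STAI-6 points per year. The spurious shift runs from 5 × 0.05 = 0.25 to 10 × 0.2 = 2.0 points, or 6 to 50% of the 4-point range.

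**(a) Unadjusted ANOVA, N = 1195.** With three of six groups shifted, f = 0.5 × shift / 12.

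| Shift (points) | f | λ | False-positive rate |
|---|---|---|---|
| 0.25 | 0.0104 | 0.13 | 5.6% |
| 1.2 (8 years × 0.15) | 0.0500 | 2.99 | 22% |
| 2.0 | 0.0833 | 8.30 | 58% |

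For one pair at 1.2 points, SE = 12 × √(2/199) = 1.20 and the rate is 17%.

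**(b) Would the screen catch such an age gap?** Assume an age SD of 10 to 11.5 years. A 5-year gap in three groups gives f = 0.5 × 5/10 = 0.25 down to 0.5 × 5/11.5 = 0.217. The screen misses it at most 0.3% of the time at N = 673 and less than 0.001% of the time at N = 1195. At 8 to 10 years the miss rate is effectively zero.

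**(c) What the screen does miss.** One group off by 0.2 SD on a covariate: f = 0.2 × √(5/36) = 0.0745, λ = 6.64, flagged 47% of the time at N = 1195. If the covariate correlates 0.2 to 0.3 with anxiety, the bias is 0.2 × 0.2 × 12 = 0.48 to 0.2 × 0.3 × 12 = 0.72 points. Left unadjusted, with f = (bias/12) × √(5/36) = 0.0149 to 0.0224, the omnibus false-positive rate is 6.2 to 7.8%.

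**(d) Simulation of the three analyses.** 1500 runs per cell; groups 2 to 5 younger by 0.2 to 0.5 SD; correlation 0.2 to 0.3; N = 672 and 1194. Simulated false-positive rates were:
- no covariate: 6.5 to 44.3%;
- age entered only if flagged: 4.4 to 6.2%;
- age always entered: 4.4 to 6.2%.

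Under these assumptions, an unadjusted primary test does most of the harm. The screen adds little when its result is always acted on.

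**The case against.** The strongest reply is that the natural reading of the text is that flagged variables will be controlled. On that reading, step (b) shows that an age gap large enough to matter would almost never be missed, and step (d) shows an error rate near nominal. This is right as far as it goes: the 6 to 58% range must not be read as the expected error of the plan. It applies only if age is left out of the model. But the protocol does not commit to entering flagged variables, and the named primary model contains none.

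A reader might infer that the protocol itself establishes that age drives both HPV positivity and anxiety. It does not. The anxiety link is reported as a suggestion from earlier research, and only among HPV-positive women. No link is stated for HPV-negative or cytology-only women, and a link confined to HPV-positive women could be effect modification. What stands is a prior reason to suspect age.

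A reader might also infer that the group difference could be an area difference, because group 6 exists only since "the participating sites have not yet introduced HPV primary screening for all women". No section links deprivation or site to HPV result or to anxiety. Setting the numbers per group "proportionate to the numbers of results processed at each laboratory" would, if followed, tend to balance groups across sites. Deprivation and site are plausible confounders and no more.

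Finally, an article condenses a fuller document, and the exact covariate list may be given there. That would excuse silence. Here the article states a selection rule, and the rule is a weak one. The stated limit on causal inference does not repair it.

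**Conclusion.** The point holds as a weakness of the stated method. Covariates for a non-randomised primary comparison are chosen by tests of imbalance, remain optional, and are absent from the named model, although age is a foreseeable candidate. Its size depends on how the rule is applied. With age left out, false-positive rates are 6 to 58% for shifts of 0.25 to 2.0 points. With every flagged variable entered, they stay near 5%. For the modest imbalance that the screen misses about half the time, the cost is 0.5 to 0.7 points of bias and a rate of 6 to 8% when unadjusted. The age gaps, slopes, correlations and age SD are all assumed, because the protocol gives none of them. The main risk is therefore the missing commitment to adjust, more than the sensitivity of the screen. The change should be made, since it removes that freedom at almost no cost.

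**What to change.** Specify the primary models for STAI-6 and GHQ-12 as result group adjusted for age (continuous, allowing curvature), IMD score and site, whatever the preliminary tests show. Carry the same three covariates into the over-time and secondary models. Report the unadjusted ANOVA as a supportive analysis. Keep the preliminary ANOVAs and chi-square tests as description, and remove their role in choosing covariates.

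The cost is analysis wording and a few degrees of freedom out of about 1195 responders. No new data are needed: under Procedures and Descriptive measures, age, IMD score and site already come from the NHS records or laboratories.

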### Sample size

The study has been powered to detect a small-to-medium between-group difference (f=0.14) in anxiety (as measured by the STAI-6).^11^ On the basis of previous studies,^11^
^12^ we expect anxiety scores across groups to be in the range of 36–40, with an SD of 12. With an α of 0.05, a sample size of 673 will give us 80% power to detect a between-group difference in anxiety.

Assuming an initial response rate of 35%, with 75% of initial responders returning a second questionnaire at 6-month follow-up, and 75% of responders at 6 months completing a third questionnaire at 12 months, we plan to approach 3415 participants to achieve the target sample size. Response rate will be monitored as the study progresses so that the number of women approached at baseline can be adjusted if the response rate is higher or lower than expected (within our funding constraints).

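### The mixed ANOVAs over baseline, 6 and 12 months would in standard form use only three-questionnaire completers (about 672 of 1195 responders); a linear mixed model on all responders is a cheap improvement

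*Protocol article*

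**What the plan says.** Under Data analyses and statistics, the protocol article separates two analyses of anxiety and distress. The primary one is at baseline: "Primary analyses will comprise between-groups ANOVAs to explore whether anxiety and general distress differ between screening result groups" shortly after the result is received. The longitudinal one is: "Mixed ANOVAs will be conducted to explore whether differences in anxiety and general distress are observed between screening result groups over time", with baseline, 6 and 12 months as the occasions. The Abstract describes the framework for group differences and change over time as general linear modelling. No likelihood-based mixed model or imputation is mentioned.

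Under Sample size, attrition is planned for: "Assuming an initial response rate of 35%, with 75% of initial responders returning a second questionnaire at 6-month follow-up", followed by "75% of responders at 6 months completing a third questionnaire at 12 months". On that basis, "we plan to approach 3415 participants to achieve the target sample size". The target is 673, so it is a count of women who have returned the third questionnaire.

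**The concern.** A conventional mixed (split-plot) ANOVA needs a complete row of outcomes for each woman. If she misses one wave, the questionnaires she did return are lost to that analysis. The plan expects more than two in five baseline responders to miss at least one wave, so the choice of method decides whether a large share of the collected data contributes to the over-time answer.

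Completers may also differ from the other women in their anxiety. The Introduction describes different pathways by result: immediate colposcopy for HPV-positive women with abnormal cytology, a 12-month recall for those with normal cytology, and routine recall for HPV-negative women. Reasons to keep replying could therefore differ by group. The Discussion expects adverse effects to be small and short-lived. If anxious women stop replying, completer means move towards that expectation; if reassured women stop replying, they move away from it. The second planned paper rests on these analyses.

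**Working it through.** **1. The plan's own figures.** Inputs are from Sample size: 3415 approached, 35% response, then 75% and 75% retention.

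- Baseline: 3415 × 0.35 = 1195.3
- 6 months: 1195.3 × 0.75 = 896.4
- 12 months: 896.4 × 0.75 = 672.3, against the stated 673. In reverse, 673 / (0.35 × 0.5625) = 3418, against the stated 3415.

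The chain reproduces. The power statement does too: a one-way ANOVA with six groups, f = 0.14 and α = 0.05 gives 80.9% power at N = 673. The baseline ANOVA on 1195 women would have 97.7%.

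**2. What a completer analysis leaves out.**

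- Women: 1 − 0.75² = 43.75%; 1195.3 × 0.4375 = 523.
- Questionnaires returned: 1195.3 + 896.4 + 672.3 = 2764. Used: 3 × 672.3 = 2017. Unused: 747 (27%), made up of 523 baseline and 896 − 672 = 224 six-month questionnaires.

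The retention chain counts as 12-month responders only women who also replied at 6 months. A woman who skipped the 6-month pack but returned the 12-month one would also be dropped.

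**3. Possible bias, mechanism in one group only.** SD 12 is from Sample size, and 56% retention follows from it. Assumed, and not in the article: correlation 0.55 between baseline and 12 months, and odds of staying that fall 1.5-fold per SD of baseline anxiety in one group and not in its comparator.

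- Shift in that group's completer mean at baseline: −2.05 points
- Shift at 12 months: 0.55 × (−2.05) = −1.13 points
- Error in the group-by-time contrast: 2.05 − 1.13 = about 0.9 points

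The article expects group means between 36 and 40, a spread of 4 points.

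**4. Same mechanism in every group.** With group means of 40 and 36 and the same odds ratio in both, the completer contrast is off by about 0.15 points at baseline and 0.08 at 12 months. The group-by-time error is below 0.1.

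**5. Main effect of time.** With an assumed correlation of 0.5 and log-odds of dropout of 0.25 to 1.0 per SD of baseline anxiety, completer means are too low by 1.3 to 4.3 points at baseline and 0.6 to 2.2 at 12 months. Change over time is off by about 0.7 to 2.2 points. An analysis that carries the observed baseline through, as a likelihood model does, has a bias of about 0 under this mechanism.

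**6. Precision.** With p = 0.5625 retained and baseline-to-12-month correlation r, the gain in effective sample size at 12 months is (1/p) / [(1 − r²)/p + r²]. This gives 1.08, 1.12 and 1.19 for assumed r of 0.4, 0.5 and 0.6.

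**The case against.** The strongest reply is that the article never says incomplete cases are deleted. It gives no analysis set and no missing-data rule, it is a condensed document, and such rules are often left to a fuller plan. A mixed ANOVA can also be run after imputation or on long-format data. This stands in part: completer use is an inference. It rests on the named method in its usual form, the general linear modelling label in the Abstract, and a target counted after the third questionnaire. The suggestion is to change the named method, not to write down a missing policy.

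Several stronger readings are tempting, and the document does not support them:

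- *The primary result is compromised.* It is not. Women lost later still enter the baseline ANOVA.
- *The study is underpowered.* It is not. The 673 is already net of both retention steps.
- *A completer analysis is valid only if dropout is completely at random.* That is too strong for group contrasts. Dropout that differs by group but is unrelated to anxiety within group does not bias them, and an anxiety-related mechanism common to all groups largely cancels (step 4).
- *The contrast of interest could be wrong by 2 points.* That figure is the completer contrast at baseline, which the primary ANOVA estimates on all responders. The group-by-time error in the same scenario is about 0.9, and the scenario is deliberately one-sided.

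It is also fair to say that the remedy is partial. The Procedures section provides clinical-record data on all women approached, and the article acknowledges self-selection. Those provisions are aimed at initial non-response; they could help describe women lost later, but they do not bring those women's answers into the mixed ANOVA.

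**Conclusion.** The point holds as a worthwhile improvement to a non-primary analysis, not as an error that must be corrected for the study to stand. In standard form the named method would leave out about 523 of 1195 responders and 27% of returned questionnaires; those counts follow from the plan's own figures. That it would be applied this way is inferred.

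Bias is a risk, not an established fact. The main effect of time is exposed if dropout depends on anxiety. The group-by-time contrasts are exposed only if that dependence differs between groups: about 0.9 points under the one-group assumption, near zero under a common mechanism. No figure in the article shows which pattern to expect. The precision gain from using all responders, about 8% to 19% in effective sample size at 12 months, depends on assumed correlations of 0.4 to 0.6.

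**What to change.** Replace the mixed ANOVAs with a linear mixed model for each of anxiety and distress: fixed effects for group, time and group × time, relevant covariates (including any that predict dropout), an unstructured within-woman covariance, and REML estimation. Fit it to every woman with at least one questionnaire and report the group contrasts at each time point. Keep the three-wave completer mixed ANOVA as a sensitivity analysis.

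The cost is a change of wording and slightly more analysis work. SPSS, R and Stata, all named in the article, fit this model, and no extra data are needed. The model relies on dropout being missing at random given what has been observed. Dropout driven by current, unrecorded anxiety would remain a limitation to state in the report, and the initial non-response is not addressed by this change.
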